### Randomisation

The cluster of intervention, and thus the unit of randomisation, was the commune and its corresponding health station. Probability proportional to size sampling (PPS) based on the total number of live births at baseline (2005) was used. Randomisation continued until one arm had reached over 50% of the total amount of live births. This resulted in 44 out of 90 clusters being allocated to intervention (Figure 2). Randomisation was performed by the research team.

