### Participants

Districts with a NMR higher than 15/1000 were selected to compose the study area, resulting in eight out of 14 districts in the province (Figure 2). In 2005 there were 6251 live births and 151 neonatal deaths in these districts, resulting in a total NMR of 24/1000. These districts were composed of 90 communes with a number of live births ranging from 7 to 270 and neonatal deaths between 0 and 6 (2005). All the 90 communes with a corresponding CHC in the study area were eligible for inclusion, based solely on their geographical location. All newborns delivered within the study area and period were included.

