### Sample size

Power calculations for sample size were based on neonatal mortality being a primary outcome measure. The design effect was assumed to be 1.5 for the purpose of sample size calculation. Given the level of current neonatal mortality of 24/1000 in 2005 the study size has sufficient power to demonstrate a significant reduction of 7/1000 and more over the three year study period, i.e. to 17/1000 or less (alfa 0.05, beta 0.2). Using a case-referent approach for the evaluation a three-year sample of neonatal deaths (450 cases) and randomly selected referents, 6% from the total population of live births (1120 referents), will allow to demonstrate an effect of the randomised intervention of 26% (OR 0.74, 95% CI 0.55-0.99).

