#### Healthcare process and primary outcome

The healthcare process will be analysed at individual level, using the case-referent design previously described. By applying a case-referent design it will be possible to adjust for possible confounding. The primary outcome, neonatal mortality, which also will be analysed at individual level, comparing the intervention and control area using surveillance data as well as case-referent data. These analyses will use statistical techniques to account for the cluster design as suggested by Campbell et al, with an appropriate adjustment for design effect [38].

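### The Randomisation section does not say how probability proportional to size entered the assignment, the 44 of 90 split fits one reading poorly, and commune size is absent from the stated mortality comparison

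*Protocol article*

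**What the plan says.** The Randomisation section of the protocol article makes the commune the unit of allocation and gives the method: "Probability proportional to size sampling (PPS) based on the total number of live births at baseline (2005) was used". It then gives a stopping rule, "Randomisation continued until one arm had reached over 50% of the total amount of live births", and the outcome, "This resulted in 44 out of 90 clusters being allocated to intervention". The arm that reached half is not named.

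The Participants section supplies the sizes: "In 2005 there were 6251 live births and 151 neonatal deaths in these districts, resulting in a total NMR of 24/1000". It describes the study area as composed of "90 communes with a number of live births ranging from 7 to 270". The distribution between these limits is not given.

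Under Data analysis, the section on healthcare process and primary outcome plans an individual-level mortality analysis "comparing the intervention and control area using surveillance data as well as case-referent data", with techniques that account for clustering and a design-effect adjustment. It says the case-referent design makes adjustment for confounding possible, but names no covariates. Commune size and allocation probability do not appear.

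**The concern.** Sampling with probability proportional to size (PPS) is a way to select units. Used to allocate treatment, it can mean two different things, and the section does not say which.

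- **Reading 1: size sets assignment.** Communes are drawn by PPS into the intervention arm until it holds over half of the births, and the rest become controls. The chance of receiving the intervention then rises with commune size, and the arms differ in size by design.
- **Reading 2: size sets only the order.** Communes are drawn in PPS order, each drawn commune goes to either arm by chance or alternation, and once one arm passes half the remainder go to the other. Each commune then has about an even chance.

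The difference matters because adjusting for clustering corrects the standard error, not an imbalance between arms. If reading 1 applied and small communes had different mortality, the surveillance comparison would carry a size effect that the stated analysis does not remove. Under either reading, a reader cannot verify the allocation probabilities from the text.

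**Working it through.** **Inputs from the article.** 90 communes; 6251 live births and 151 neonatal deaths in 2005; commune sizes 7 to 270; 44 intervention communes, hence 90 − 44 = 46 controls; planned fall from 24 to 17 per 1000 (Sample size section).

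**Assumed.** The size distribution (lognormal, with the range and total held), shown over a range of CVs, and the relation of size to mortality.

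**Step 1: average size per arm.** The rule leaves each arm with about half of the births: 6251/2 = 3125.5.
- Intervention: 3126/44 = 71.0 births per commune.
- Control: 3125/46 = 67.9 births per commune.

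These shift slightly with the overshoot of the last commune drawn, or if control was the arm that passed half. The overall mean is 6251/90 = 69.5.

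**Step 2: can the described procedure give 44?** Simulated number of intervention communes, 1000 runs per cell, so the smallest probabilities are rough:

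| Assumed size CV | Reading 1: mean | Reading 1: P(44 or more) | Reading 1: mean size, intervention vs control | Reading 2: mean (95% range) | Equal-probability draws: mean |
|---|---|---|---|---|---|
| 0.42 | 41.5 | 0.10 | 76 vs 64 | 45.1 (41–49) | 45.5 |
| 0.56 | 38.1 | 0.004 | 84 vs 59 | 45.0 (38–53) | 45.5 |
| 0.73 | 33.8 | <0.001 | 95 vs 55 | 44.9 (33–56) | 45.6 |

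At a CV of 0.67, reading 1 gives about 35 communes and P(44 or more) of about 0.1%. If control was the arm filled by PPS, its 46 communes fit worse still (about 1% or less).

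**Step 3: the exception.** The smallest spread the range allows is one commune of 7, one of 270 and 88 of (6251 − 277)/88 = 67.9, a CV of about 0.32. With the largest commune drawn, 270 + 42 × 67.9 = 3121.8 is just short of 3125.5, so a 44th commune is needed. Reading 1 can therefore give 44, but only with nearly uniform sizes.

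**Step 4: allocation probability.** At a CV of about 0.7, reading 1 gives about 0.06 for the 7-birth commune and 0.89 for the 270-birth commune. Reading 2 gives 0.48 to 0.51 across sizes.

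**Step 5: effect on the mortality contrast with no true effect.** Suppose communes below median size have 1.5 times the mortality of the rest.
- Reading 1, averaged over all draws: rate ratio 0.91 (CV 0.56) or 0.89 (CV 0.73). For mortality ratios of 1.25 and 2, the results are 0.95 and 0.84 (CV 0.56), or 0.94 and 0.82 (CV 0.73).
- Reading 1, keeping only draws with exactly 44 communes: 0.970 (CV 0.4), 0.975 (CV 0.6) and 0.975 (CV 0.7, few such draws).
- Equal-probability draws with exactly 44 communes: about 0.98.
- Reading 2, over all draws: 1.00.

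The planned effect is 17/24 = 0.71, a 29% reduction. The distortion for the split that occurred is 2 to 3%.

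**The case against.** The strongest case against is that this is only a reporting ambiguity. The article speaks of one arm reaching half, not of the intervention arm, so reading 2 fits the words, and under it 44 is unremarkable and nothing needs correcting. Covariates are commonly left to a full protocol or analysis plan that is not shown, and the participant-flow figure, also not available here, may give births per arm. Most of this stands.

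A reader might infer three stronger conclusions. The documents support none of them.

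- **That the analysis treats allocation as equal-probability.** The article never says so; this would be an inference from silence. It also leaves room for confounder adjustment in the case-referent analysis, which is part of the primary evaluation.
- **That the mortality contrast is biased by design by about a third of the planned effect.** That size comes from averaging reading 1 over allocations with clearly fewer intervention communes than 44. The split that occurred is near balance on size (71 vs 68). The better 44 tells against size-driven assignment, the less confounding remains. No section links commune size to mortality; the reported district differences and distance decay are not given by commune size.
- **That the split proves the stated method was not used.** It fits reading 2, and reading 1 at minimal spread.

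What the objection does not remove is that the section states a size-based method positively without describing the step that assigned the arm, and that the surveillance comparison names no adjustment for the variable that drove the draw.

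**Conclusion.** The point holds as a defect of description with a cheap analytic safeguard, not as a demonstrated bias. The allocation mechanism cannot be recovered from the Randomisation section. If PPS set assignment to intervention, 44 of 90 is unusual unless commune sizes vary little; if PPS only ordered the draws, 44 is ordinary. The split leans towards the second.

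For the realised 44/46 split, the likely distortion of an unadjusted comparison is a null rate ratio of about 0.97 to 0.98. This rests on two assumptions the documents do not supply: the shape of the size distribution and a 1.5-fold mortality ratio for communes below median size.

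**What to change.** 1. Correct the Randomisation section to state how PPS entered the assignment (chance of entering intervention, or drawing order only), how a drawn commune was given its arm, which arm passed 50%, and the 2005 live births in each arm.
2. Include the log of each commune's 2005 live births as a covariate in the primary mortality model. The randomisation used this figure, so it is already held for all 90 communes. The cost is one commune-level degree of freedom.
3. Use inverse-probability weighting only if it is confirmed that assignment probability depended on size. The weights cannot be built while the mechanism is unclear, and under reading 2 they are not needed.

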### Data analysis

#### Intervention process

The intervention process will be analysed at cluster level. Qualitative analyses of the intervention process, through methods described above, are to be performed through content analysis. Quantitative data, like meeting attendance and frequency and measurements of knowledge level among health staff will be analysed to estimate the effect of the intervention.

#### Healthcare process and primary outcome

The healthcare process will be analysed at individual level, using the case-referent design previously described. By applying a case-referent design it will be possible to adjust for possible confounding. The primary outcome, neonatal mortality, which also will be analysed at individual level, comparing the intervention and control area using surveillance data as well as case-referent data. These analyses will use statistical techniques to account for the cluster design as suggested by Campbell et al, with an appropriate adjustment for design effect [38].

### Time plan

The project, which has been given the acronym NeoKIP (Neonatal health - Knowledge Into Practice) started in autumn 2005 by negotiations with provincial health authorities and representatives of the WU in Quang Ninh. Baseline data collection, covering year 2005 data, was performed in 2006. The facilitation intervention was initiated in July 2008 and continued until June 2011. Analysis of the intervention process is ongoing and analyses of outcome data will take place in 2011-12.

### Dissemination of project results

Previously published results from the NeoKIP project has reveled a substantial under-reporting of neonatal deaths, with a NMR at baseline being four times higher than what was officially reported [41]. Baseline investigations also found a strong correlation between home deliveries and neonatal death [39] and that 25% of the newborns that died during 2005 did not have any contact with the health system prior to death [42]. In the baseline study we used the knowledge assessment questionnaire mentioned above in a survey, with results indicating a clear potential for improvement in basic neonatal knowledge at primary healthcare level [43]. Focus group discussions with primary healthcare staff during the baseline study indicated that primary healthcare staff work in a context that only to some extent enables them to translate knowledge into practice [44].

Furthermore, analyses of data collected during the intervention period has demonstrated that ethnic minority mothers are at increased risk of experiencing a neonatal death [45] and that there is marked distance decay in delivery care utilisation in this setting [46], indicating target areas for the intervention.

Future results from the trial will be published in peer-reviewed international journals and presented at international conferences. The findings and its implications has been and will continue to be reported to and disseminated through the Ministry of Health in Vietnam. Results will be taken into consideration for future policy and planning. The approach addressing this kind of intervention to an existing healthcare system has not been scientifically studied before in a resource poor setting and the results will be of great interest for the public health community. Finding ways to make progress can be anticipated to have a global audience.

### Ethical considerations

Participating in the study can involve stressful moments for participating families as families having neonatal deaths will be visited for an interview. Informed consent will be asked from all families before interviews and all staff within the project will work under confidentiality to protect respondents. Anonymity of subjects was secured through depersonalisation of data at an early stage of data handling. The study was approved by the Ministry of Health in Vietnam, the Provincial Health Bureau in Quang Ninh and the Research Ethics Committee at Uppsala University, Sweden (Dnr 2005:319).

## Discussion

To find effective and feasible methods of knowledge translation in order to improve maternal and newborn health and survival is a global research priority and essential for reaching the Millennium Development Goals 4 and 5. A lot of attention has been given to community participation as a driving force of change, and trials with women's groups have shown encouraging results in relation to neonatal survival [18,19]. There is however an equally great need to find ways to scale up interventions of knowledge uptake that have been proven effective in a relatively small sample considering the magnitude of the problem. The successful trials in Nepal and India have been performed with a high coverage and intense activities in the intervention clusters. In order for this approach to be scaled up it will need to be carried out in existing health systems. Therefore, our study intends to evaluate a method of knowledge translation which is less resource and time demanding and that can be applicable within incumbent healthcare structures.

Previous studies using community-based participatory approaches in order to improve neontal survival have been situated in settings with a rather high NMR. The panorama of causes of neonatal death and the subsequent means for averting them differs between different strata. In high-mortality settings there will be a larger proportion of deaths due to infections, and community-based interventions like the recognition of danger signs and improved care seeking patterns is a priority, whereas health system strengthening interventions like access to emergency obstetric care (EmOC) will be needed in order to lower NMR further in settings in the lower NMR strata. Our study is set in a setting with a NMR well below the global average, but still in an interval where community-based interventions is expected to be needed for improving neonatal survival. As such, the present study fills a scientific gap not only in the Vietnamese setting but is of global interest.

The intervention approach - team based facilitation - was informed by the PARIHS framework and adapted to the Vietnamese context. At a first instance it might look odd to apply a "bottom-up" approach in a context like the Vietnamese which is characterised of "top-down" gouvernance. However, testing this approach was met by enthusiasm in the project team and other Vietnamese stakeholders. A pilot study further indicated that facilitation was feasible and promising as an intervention. The concrete shape of the intervention was developed and performed by the Vietnamese collaborators. Issues like who to include in the groups that would receive facilitation and who that would be a suitable facilitator were carefully considered, having the opportunities to upscaling in mind. Thus, in the evaluation stage of the study we put particlular emphasis on understanding how the facilitation intervention is working in this specific Vientamese context. A great deal of the data collection is about shedding light on how the facilitators perform their role and how they are perceived by involved stakeholders. While we explicitly have used the PARIHS framework to design the study we will be able to provide feedback on how this model works, particularly the facilitation cornerstone, in a cultural context different from where the framework was developed.

Additional to this professional approach, the current project has a profound gender perspective. It recognises the local gender power structure within which women live and which may circumvent their ability to improve health practices. It acknowledges the vital role of mothers as actors in improving their own and their newborns' health. The majority of the healthcare workers responsible for perinatal care at primary level are women. By employing female facilitators (women recruited from the local WU) to empower local health workers and the mothers, the project takes advantage of a shared female knowledge and agency across the main actors involved in the intervention. We believe this combined professional and female actor's focus increases the potential for successful outcomes and sustainable effects.

The findings will not only be of interest in Vietnam and other countries with a similar healthcare context, but also in high-income settings. Rapidly increasing costs for health care, enhanced demands from the patients, and an exponentially growing knowledge base for health care makes it necessary to develop evidence-based interventions for knowledge uptake. The global relevance of effective knowledge translation strategies and the potential for substantial improvements of people's health make it urgent to accomplish well designed studies in this field.
